### **10.3.7 Trial expectations**

*T1, process evaluation.*

Information about the participants expectations about parent training in general as well as the specific expectations about the STEPS app will be collected using a questionnaire developed specifically for the study (see Appendix 2). Parent will be asked to rate the statements on the Likert-type scale as well as to provide open-ended text responses.

### **10.3.8 Experience of parenting**

*T1, T2, T3, T4, T5, process evaluation*

This will be measured with open-ended questions: “Think of a memorable interaction that you have had with your child within the last 24 hours. Tell us about that interaction. For example, what went well and why or what went badly and why? What might you do differently next time?”

### **10.3.9 Adverse events**

*T1, T2, T3, T4, T5, safety outcome.*

This will be measured with the Medical and psychological events and difficulties questionnaire (MAPED), which has been developed for the study (see Appendix 3). Parents will be asked to report retrospectively any physical and/or mental health difficulties they or their child have experienced in the last three months. They will also be asked to report any difficulties they or their child have had with daily activities. These will be used to monitor safety and to provide descriptive information about adverse events experienced during the trial.

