## 8. Eligibility criteria

### 8.1 Inclusion Criteria

- Parents of all new referrals of children aged 5 years 0 months to 11 years and 11 months that have been accepted onto the assessment waiting list and their referred children. A 'new referral' is defined as a child who has been on a waiting list for assessment for no longer than nine calendar months. This will be confirmed through screening medical records.
- Parents aged 18 years or older: confirmed through screening.

The electronic version of this document is the latest version. It is responsibility of the individual to ensure that any paper material is the current version. Printed material is uncontrolled documentation.

- Child screened positive for high levels of hyperactivity/impulsivity, inattention, and conduct problems: Child scored  $\geq 8/10$  on the hyperactivity/inattention and  $\geq 4/10$  on the conduct problems subscale of the SDQ, established through screening medical records. These cut-offs identify the top 10% of the population (Youth In Mind)
- English language competence: parent confirms through screening.
- Access to a STEPS compatible mobile device (iOS 9.0 or later; Android 4.1 or later) with access to the internet (i.e., mobile internet or wi-fi); parent confirms through screening.

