## 21. Harms

### 21.1 *Specification, Timing and Recording of Safety Parameters*

Please see section 21.2 below for adverse event definitions and reporting parameters. The risk of participants experiencing any adverse events during this trial as a result of using STEPS is very low. Adverse events concerning parental or child physical and mental health will be monitored throughout the trial. Any physical or mental health difficulties spontaneously disclosed by a parent in their communication with researchers will be entered into the Red Pill database using the OPTIMA adverse events form created specifically for the study (see Appendix 4). Moreover, at each timepoint, participants will be asked to complete a formal questionnaire on adverse events (Medical and psychological events and difficulties questionnaire) that happened to them and their child. This information will be collected online using ePRO. The forms will be reviewed regularly, and all adverse events will be recorded on the OPTIMA adverse events form in the Red Pill database. All participants that experience a serious adverse event will be followed-up by the researchers, who have completed Level 2 safeguarding training, until the event is resolved. Where necessary, the participant's clinical service which accepted the referral will be informed about the event.

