#### Family dynamics:

- Deterioration in child behaviour (including self-harm) or wellbeing.
- Deterioration in sibling wellbeing (including self-harm).
- Increased family discord.
- Breakdown in family structure.
- Social work involvement or child protection concerns.

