**NO: go to Q3**

**YES**

- Please say a bit more about the problem [500 characters]
- When did this problem start? Please provide approximate date.
- When did this problem end? Please provide approximate day or select 'ongoing' if not resolved.
- Did this problem result in hospitalisation? **Yes/No**. If yes, please describe [500 characters].

This section will ask about any **mental health** or **behavioural** problems. We will first ask about **your child** and then ask about **you**.

3. Has your child had any **mental health** or **behavioural** problems in the last 3 months?

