**NO: go to Q4**

**YES**

- Please say a bit more about the problem [500 characters]
- When did this problem start? Please provide approximate date.
- When did this problem end? Please provide approximate day or select 'ongoing' if not resolved.
- Did this problem result in hospitalisation? **Yes/No**. If yes, please describe [500 characters].

4. Have you had any **mental health** problems in the last 3 months?

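### The adverse event questionnaire never asks whether an ongoing problem has got worse, and sibling harm has neither a question nor a code, although section 21.3 lists both kinds of harm for reporting

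*Protocol*

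**What the plan says.** Section 8.1 makes behaviour problems a condition of entry: "Child screened positive for high levels of hyperactivity/impulsivity, inattention, and conduct problems", meaning an SDQ hyperactivity score of at least 8 and a conduct score of at least 4.

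Section 10.3.9 schedules MAPED at T1 to T5 as the safety outcome and describes it as follows: "Parents will be asked to report retrospectively any physical and/or mental health difficulties they or their child have experienced in the last three months". In Appendix 3 the child behaviour question reads "Has your child had any mental health or behavioural problems in the last 3 months". A positive answer to any of questions 1 to 6 leads to a free-text box ("Please say a bit more about the problem [500 characters"), a start date ("When did this problem start? Please provide approximate date") and an end date or ongoing status. Questions 1 to 4 add "Did this problem result in hospitalisation".

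Section 21.1 says that completed forms are reviewed and that "all adverse events will be recorded on the OPTIMA adverse events form in the Red Pill database". Section 21.3 lists the expected adverse events, among them "Deterioration in child behaviour (including self-harm) or wellbeing" and a matching entry for siblings, and says that they will be reported in the main publication.

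**The concern.** Most harms in section 21.3 are changes: deterioration, or an increase in something. The instrument meant to solicit them asks about presence. In a population selected for conduct problems, a truthful parent may well report a behavioural problem at baseline and at later visits, whether the child is better, the same or worse. If worsening is not asked for, its recording depends on what each parent chooses to write, and that can differ between families and between arms that are not blinded.

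At stake is the completeness of the adverse event record for an unguided app with no personal clinical support (section 9.1). That record goes to the Data Monitoring Committee and is the source for the events promised in the publication. A later analysis plan cannot recover an answer that the form did not request.

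**Working it through.** The protocol gives no figure on this point, so the check sets the passages side by side.

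**Step 1: what section 21.3 lists.**

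| Group | Listed | Change of degree | Discrete event |
|---|---|---|---|
| School/community | 2 | 1 (school or activity refusal) | 1 (exclusion) |
| Family dynamics | 5 | 3 (child, sibling, family discord) | 2 (family breakdown; social work or child protection involvement) |
| Parent wellbeing | 4 | 4 (mood, anxiety/stress, fatigue, sleep) | 0 |
| Total | 11 | 1 + 3 + 4 = 8 | 1 + 2 + 0 = 3 |

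The 3 discrete events can be reported with dates under questions 5 and 6. The 8 changes of degree need a comparison with an earlier state.

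**Step 2: what the form returns for three children who all answer yes to question 3 at T2.**

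| Field | A: long-standing, unchanged | B: long-standing, clearly worse since T1 | C: began after randomisation |
|---|---|---|---|
| Problem in last 3 months | yes | yes | yes |
| Start date | before randomisation | before randomisation | after randomisation |
| End date | ongoing | ongoing | ongoing |
| Hospitalised | no | no, unless extreme | no |
| Free text | unprompted | unprompted | unprompted |

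C is separable from A by start date, and the T1 MAPED confirms it. B is not separable from A by any structured field. Only the free text can tell them apart, and it does not ask about change.

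**Step 3: whether a later stage restores the distinction.** The definition in section 21.2.1 refers to an untoward occurrence and does not mention baseline. The form in Appendix 4 records description, category, start and end dates, outcome (resolved, resolved with treatment, ongoing), relatedness, expectedness, seriousness and who is involved. It has no field for change from baseline and no severity rating. No section says when a continuing pre-existing problem becomes an adverse event.

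**Step 4: siblings.** Section 21.3 lists deterioration in sibling wellbeing, including self-harm. Section 21.1 speaks of monitoring parent and child health. MAPED asks about the referred child and the parent. Questions 5 and 6 touch on relationships with household members, but not on a sibling's own wellbeing. Field 12 of the adverse events form offers the target child or the target parent only. The harm is listed for reporting but is neither specifically asked about nor codable.

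**The case against.** The best defence is that the system holds more than the opening questions. Dates are requested for every reported problem and a baseline MAPED exists, so new onset is identifiable. Question 7 asks whether the difficulties raised concerns about taking part, hospitalisation is asked in questions 1 to 4, and spontaneous disclosures are also entered (section 21.1). Child behaviour is scored on SNAP-IV ODD at T1 to T5 and compared by arm at four follow-up times (section 19.1), so an average worsening under STEPS would show in the efficacy results. CHU9D and EQ-5D-5L are collected at all five times. All of this stands, and it limits the point.

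A reader might infer three stronger claims, none of which the documents support:

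- That the deterioration harms cannot be detected, or would be hidden from the Data Monitoring Committee. The routes above are partial but real.
- That the presenting condition would be logged as an adverse event in nearly every child, leaving both arms close to ceiling. Section 21.1 has forms reviewed before events are recorded, and section 21.2.1 ties an adverse event to a subject who has been given a therapy. A T1 report on the months before entry does not clearly meet that definition.
- That the trial would base a safety conclusion on raw yes counts by arm. Section 10.3.9 promises monitoring and descriptive information, and no such test is planned. Any p-value or power figure for it would rest on invented rates.

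What the defence does not reach is child B above. Start dates do not separate that child from child A, and hospitalisation finds only extremes. A mean SNAP-IV difference can hide a worsening subgroup and does not cover parent mood, family discord or siblings. The protocol assigns none of these scales to safety.

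**Conclusion.** The point holds in a limited form. Worsening of a pre-existing problem, which section 21.3 treats as a harm to be reported, enters the adverse event system only if the parent volunteers it. Sibling deterioration is listed there with no question and no code.

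The gap concerns the 8 of 11 listed harms that are changes of degree, one of which is the sibling item. Within those 8 it applies to problems already present at entry; new-onset problems in the child or parent can be identified. The documents do not allow an estimate of how many events would be missed, and none is offered. The conclusion rests on the wording of the forms and on the entry criteria. It assumes only that some entry problems continue into follow-up. The sample size and the primary analysis are unaffected. The change is worth making because it is cheap and improves the safety record.

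**What to change.** 1. At T2 to T5 keep questions 1 to 6 as they are. After each positive answer add one item asking whether the problem is new, worse or unchanged since the last questionnaire and since before the study. Add a matching field to the adverse events form.
2. State in section 21.2.1 that the T1 MAPED is the baseline reference, and that a reported problem counts as an adverse event only if it is new since T1 or worse than at T1.
3. Add a sibling prompt to MAPED and a sibling code to field 12.
4. Optionally, tabulate by arm the proportion of children whose SNAP-IV ODD score rose from T1 by a preset amount, as a descriptive between-arm safety summary. The 0.4 SD in section 13 is a difference between group means and should not serve as the threshold for deterioration in an individual child.

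The cost is one item per question on an electronic form, one form field, one code, a sentence of definition and, if wanted, one table. The drawback is a form change during the trial. Section 10.1.3 shows that participants are already enrolled, so earlier returns lack the new item and must be classified from free text and dates. Leaving the existing questions unchanged keeps the series otherwise comparable.

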## **10.4 Economic measures**

### **10.4.1 Resource-use data**

*T1, T2, T3, T4 and T5; (i) up to T2 and (ii) up to T5 contact with clinical services post-randomisation effect modifier for ODD at (i) T2 primary outcome, (ii) T5 secondary outcome.*

This will be measured using the Child and Adolescent Service Use Schedule (CA-SUS; Barrett et al., 2012), a measure applied in a range of populations of young people with mental health problems. The CA-SUS collects information on the use of all hospital and community-based health services, social care and education services, service-provided accommodation (for example, Local Authority foster or residential care), and prescribed medications for mental health conditions.

The format of the variable(s) that will be used as the effect modifier has not been yet finalised. Likely options include: hospital or community appointments related to mental health, therapy or counselling, dietician/nutritionist appointment, neurofeedback, family support worker, voluntary helpline and parent training classes (e.g., Incredible Years Parent Training, Triple P, 1-2-3 Magic, Empowering Parents, Empowering Communities) or parent support groups. We will aim to specify this in a future protocol amendment, and/or the statistical analysis plan.

The electronic version of this document is the latest version. It is responsibility of the individual to ensure that any paper material is the current version. Printed material is uncontrolled documentation.

### 10.4.2 Child's health-related quality of life

*T1, T2, T3, T4 and T5.*

This will be measured with the Child Health Utility measure (CHU9D; Stevens, 2012). The CHU9D is a paediatric preference-based quality of life measure for use in healthcare resource allocation decision-making. The CHU9D has been designed for self-report by children aged 7 to 17, but with an interviewer's help, can also be used in children as young as 6-years-old (Canaway & Frew, 2013) and guidance is available from the developers for proxy completion by parents for children aged 5 and under. The current study, however, does not involve collecting data from children and thus the CHU9D will be completed by the parents using the proxy version of the measure. The questionnaire includes 9 items, each with a 5-level response category. Each item taps into a different domain of children's present functioning: worry, sadness, pain, tiredness, annoyance, school, sleep, daily routine and activities.

### 10.4.3 Parental health-related quality of life

*T1, T2, T3, T4 and T5*

This will be measured with the EQ-5D-5L (Herdman et al., 2011). The questionnaire is used to capture general health across five domains: mobility, self-care, usual activities, pain/discomfort and anxiety/depression. Each domain has five levels (no problem, slight problem, moderate problem, extreme problem and severe problem/unable to complete activities).

Table 2. OPTIMA RCT schedule of assessments.

|                                                        | STUDY PERIOD |           |          |                   |              |     |     |                    |       |       |       |
|--------------------------------------------------------|--------------|-----------|----------|-------------------|--------------|-----|-----|--------------------|-------|-------|-------|
|                                                        | Screening    | Enrolment | Baseline | Randomisati
on | Intervention |     |     | Post-randomisation |       |       |       |
| TIMEPOINT                                              | $-T_1$       | $-T_1$    | $T_1$    |                   |              |     |     | $T_2$              | $T_3$ | $T_4$ | $T_5$ |
| Month                                                  | -1-0         | -1-0      | -1-0     | 0                 | 0-1          | 1-2 | 2-3 | 3                  | 6     | 9     | 12    |
| SCREENING:                                             |              |           |          |                   |              |     |     |                    |       |       |       |
| Screening of medical records
(HIC, age, LAC status) | X            |           |          |                   |              |     |     |                    |       |       |       |
| Screening by researcher (device,
language)          | X            |           |          |                   |              |     |     |                    |       |       |       |
| CONSENT                                                |              | X         |          |                   |              |     |     |                    |       |       |       |
| Randomisation                                          |              |           |          | X                 |              |     |     |                    |       |       |       |
| INTERVENTIONS:                                         |              |           |          |                   |              |     |     |                    |       |       |       |
| STEPS                                                  |              |           |          |                   | →            |     |     |                    |       |       |       |
| WAIT AS USUAL                                          |              |           |          |                   | →            |     |     |                    |       |       |       |
| ASSESSMENTS:                                           |              |           |          |                   |              |     |     |                    |       |       |       |
| Demographics                                           |              |           | X        |                   |              |     |     |                    |       |       |       |
| SCQ                                                    |              |           | X        |                   |              |     |     |                    |       |       |       |
| CCBS                                                   |              |           | X        |                   |              |     |     |                    |       |       |       |
| SNAP-IV (ODD)                                          |              |           | X        |                   |              |     |     | X                  | X     | X     | X     |
| SNAP-IV (ADHD)                                         |              |           | X        |                   |              |     |     | X                  |       |       | X     |
| SDQ Emotional problems*                                |              |           | X        |                   |              |     |     | X                  |       |       | X     |
| CPRS-SF (closeness subscale)                           |              |           | X        |                   |              |     |     | X                  |       |       | X     |
| PS (laxness, overactivity)                             |              |           | X        |                   |              |     |     | X                  |       |       | X     |

The electronic version of this document is the latest version. It is responsibility of the individual to ensure that any paper material is the current version. Printed material is uncontrolled documentation.

|                                  |  |  |   |  |  |  |  |   |   |   |   |
|----------------------------------|--|--|---|--|--|--|--|---|---|---|---|
| PSCS                      |  |  | X |  |  |  |  | X |   |   | X |
| CGSQ                      |  |  | X |  |  |  |  | X |   |   | X |
| CHU9D                     |  |  | X |  |  |  |  | X | X | X | X |
| EQ-5D-5L                  |  |  | X |  |  |  |  | X | X | X | X |
| CA-SUS                    |  |  | X |  |  |  |  | X | X | X | X |
| ESO child assent          |  |  | X |  |  |  |  | X |   |   | X |
| ESO                       |  |  | X |  |  |  |  | X |   |   | X |
| CODSS                     |  |  | X |  |  |  |  | X |   |   | X |
| APP USAGE:                |  |  |   |  |  |  |  |   |   |   |   |
| Number of completed steps |  |  |   |  |  |  |  |   |   |   |   |
| Other app usage events    |  |  |   |  |  |  |  |   |   |   |   |
| Trial expectations        |  |  | X |  |  |  |  |   |   |   |   |
| Experience of parenting   |  |  | X |  |  |  |  | X | X | X | X |
| Adverse events (MAPED)    |  |  | X |  |  |  |  | X | X | X | X |
| Pharmacological treatment |  |  |   |  |  |  |  |   |   |   | X |
| Clinical diagnosis        |  |  |   |  |  |  |  |   |   |   | X |
| Qualitative interviews    |  |  |   |  |  |  |  |   |   |   |   |

\*T1 SDQ emotional subscale scores will be extracted from the child's medical records, T2 and T5 SDQ will be complete online via the Sealed Envelope platform.

HIC = high levels of hyperactivity/impulsivity, inattention and conduct problems; LAC = child in local authority care; SCQ = The Social Communication Questionnaire; CCBS = Child's Challenging Behaviour Scale version 2; SNAP-IV = The Swanson, Nolan, and Pelham Rating Scale – the MTA version; ODD = Oppositional Defiant Disorder; ADHD = Attention/Deficit-Hyperactivity Disorder; SDQ = Strengths and Difficulties Questionnaire; CPRS-SF = The Child-Parent Relationship Scale- Short Form; PS = The O'Leary Parenting Scale; PSCS = The Parental Sense of Competence Scale; CGSQ = The Caregiver Strain Questionnaire; CHU9D = Child Health Utility; CA-SUS = The Child and Adolescent Service Use Schedule; MAPED = Medical and psychological events and difficulties questionnaire; CODSS = Child Oppositional and Defiance Speech Sample Scale; ESO = Etch-a-Sketch Online.

## 11. Process Evaluation

The process evaluation will follow the Medical Research Council guidelines for evaluating the implementation of complex interventions (Moore et al., 2015) and will be described in more detail in a separate protocol. Briefly, the process evaluation will use baseline and post-intervention quantitative trial data (e.g., app usage data, including counts and time) and qualitative data from semi-structured interviews with parents and clinicians (e.g., expectations, perceptions of impact, barriers to engagement) and textbox responses to open questions to explore the mechanisms for intervention implementation and impact.

All parents will be invited to respond to questions about: (1) their expectations of the trial (baseline) and (2) accounts of their experience of parenting during trial participation (T2 through to T5), see '10.3 Other measures'. This information will be collected using Red Pill online data collection platform. Detailed data on usage of the app will be automatically recorded for each participant in the STEPS arm. For details, see '10.3 Other measures'. Post-intervention, researchers will conduct remote (telephone, video call or email) in-depth, semi-structured interviews with a subgroup of parents in the intervention group (n ~ 50). Maximum variation, purposive sampling will be used to ensure that a full range of views and experiences are captured (taking account of demographic factors and levels of app engagement). In addition, telephone interviews

The electronic version of this document is the latest version. It is responsibility of the individual to ensure that any paper material is the current version. Printed material is uncontrolled documentation.

with clinicians (n ~ 10) will explore perceptions of the app and its perceived impact on preparing families for the formal clinical assessment. The interview schedules will be developed with Patient and Public Involvement (PPI) panel input. Interview data will be audio recorded and analysed using thematic analysis (Braun & Clarke, 2013), applying a framework approach (Gale et al 2013). As a thank you for taking part, all parents taking part in qualitative interviews will receive a £20 shopping voucher. There will be no incentives for clinicians.

